### Exclusion criteria

2.8

Participants who meet any of the following criteria will be excluded:

1.Participant had accompanied by severe liver, kidney, heart, brain, or lung dysfunction;2.Participant had a history of inflammatory bowel disease, or a history of colorectal cancer, or had a history of any cancer;3.Participant had a perianal abscess, anal fistula, rectal polyp, intestinal tumor, or intestinal infectious disease;4.Participant will plan pregnancy during this study;5.Participant is pregnant or lactating women at the time;6.Participant was allergic to test drugs and their ingredients;7.Participant had inability to understand the nature of the study and follow the doctor's recommendations.8.Participant will purchase or take other hemorrhoids medications during this study period.9.Participant had a history of bleeding disorders other than HD.

### Test drugs

2.9

Test drugs include *Liang-Xue-Di-Huang* Decoction granules, *Liang-Xue-Di-Huang* Decoction mimetic agent granules, diosmine and diosmine mimetic agent. All the ingredients of *Liang-Xue-Di-Huang* Decoction were listed in Table 1. The total *Chinese herbal medicine dosage* in *Liang-Xue-Di-Huang* Decoction was 54.9 g per day. These herbs in *Liang-Xue-Di-Huang* Decoction were individually cooked, filtered and pressure spray dried by pharmaceutical manufacturer to form granules. Then granules were packaged in single-dose sachets. The total granules dosage of *Liang-Xue-Di-Huang* Decoction was 10.9 g per day. *Liang-Xue-Di-Huang* Decoction mimetic agent granules was consisted of 5% *Liang-Xue-Di-Huang* Decoction granules materials, as well as maltodextrin, food coloring, and bitters. *Liang-Xue-Di-Huang* Decoction granules and *Liang-Xue-Di-Huang* Decoction mimetic agent granules were provided by Tianjiang Pharmaceutical Group Co. Ltd, Wuxi, China. Diosmine mimetic agent (0.45 g, 14 tablets) was consisted of 5% diosmine materials (0.45 g, 14 tablets), as well as maltodextrin, and food coloring. Diosmine and diosmine mimetic agent were provided by Nanjing Chia Tai Tianqing Group Co. Ltd, Nanjing, China. All these mimetic agents are as close as possible in shape, size, taste, color, and package to the real drugs.

## Interventions

3

### Experimental group

3.1

Participants in the experimental group will receive *Liang-Xue-Di-Huang* Decoction granules and diosmine mimetic agent. *Liang-Xue-Di-Huang* Decoction granules was 10.9 g per day, 1 hour after lunch and dinner, dissolving each dose in 100 ml warm boiled water. Diosmine mimetic agent, 0.45 g each time, 2 times a day, needs to be taken 2 hours after lunch and dinner meals. The course of treatment will last 7 days, unless there is a loss of follow-up. Patients will be followed up on the 7th and 14th days to learn about their medication and supplement use. The assessment that needs to be performed at visit is listed in Figure 2.

**Figure 2 F2:**
[figure not shown]
Study schedule for patients. After the enrolment and allocation, participants will receive a 7-day treatment and a 7-day follow-up. The time-points of assessment are shown in the schedule.

### Control group

3.2

Patients in the control group will be given *Liang-Xue-Di-Huang* Decoction mimetic agent granules and diosmine. The treatments and measurements will be in accordance with experimental group.

### Outcome measures

3.3

According to the latest treatment guidelines for HD,^[2]^ the primary outcome measure is the hemorrhoid bleeding score (Table 2). This score is a reliable and effective criterion for HD. The secondary outcome measure is Goligher prolapse score (Table 3) and quality-of-life score (Table 4).

**Table 2 T2:**
[figure not shown]
Hemorrhoid bleeding score (Possible Score = 0–9).

**Table 3 T3:**

Goligher prolapse score (Possible Score = 0–3).

**Table 4 T4:**

Quality-of-life score (Possible Score = 0–4).

### Emergency symptomatic treatment (serious bleeding)

3.4

If participants have the following problems during this trial, such as a large amount of ejection bleeding accompanied by a significant decrease in hemoglobin, increased heart rate, or decreased blood pressure, participants will be stop taking these medicines and hospitalized.

### Adverse events

3.5

Any adverse events, such as gastrointestinal reaction, liver damage, and renal failure will be recorded in each patient's case report form (CRF) irrespective of their relationship to the study intervention. When a severe adverse event occurs, this intervention will be immediately stopped and a detailed description of the time, severity, relationship with the drug will be recorded. Moreover, researchers will provide every necessary treatment, and report the adverse event to the Steering Committee and ethic committee of Affiliated Hospital of Nanjing University of Chinese Medicine within 24 hours.

### Safety evaluation

3.6

In China, *Liang-Xue-Di-Huang* Decoction has been used from the 19th century, and the dosage used in this study is within the recommended range based on the People's Republic of China Pharmacopeia (2015 edition). Moreover, a blood routine examination, routine urine test, liver function test, renal function test, electrocardiograph, and urine pregnancy test (women only) will be administered for safety outcomes, which are monitored both before and after clinical intervention.

### Monitoring

3.7

To ensure the quality of the trial, the monitoring data, including interim results, will be monitored by Affiliated Hospital of Nanjing University of Chinese Medicine and Jiangsu Famous Medical Technology Co., Ltd, Nanjing, China. If any issues are found, the group leader can decide to change this agreement. In addition, Jiangsu Famous Medical Technology's clinical trial expert will supervise this clinical study. The lead researcher will be solely responsible for conducting the trial and make the final decision on any changes required.

### Data management

3.8

Information from the clinical examination, as well as evaluation of treatment efficacy, will be recorded in each patient's CRF. The study record is the source document of clinical study subject and should be kept in group leader's hospital. Each center will design designated personnel to be the electronic CRF input staff. Upon completion of each subject observation, the investigator will promptly submit the study record to the CRF inputter within 1 week. The electronic CRF encoder must review whether the project record of the study notes is complete and report on time. The clinical supervisor will monitor the work of the clinical trial center at least once a month.

### Patient's privacy protection

3.9

Only researchers and arbitrator who will sign the confidentiality commitment in this clinical trial may come into contact with the participants’ personal health records. Drug regulatory departments have the right to inspect the records of clinical trials. Data will be processed anonymously, and information identifying individual subjects will be omitted. Patient's medical records will be stored in group leader's data archives.

### Statistical analysis

3.10

Frequency, median, and mean ± standard deviation of the bleeding score, Goligher prolapse score and quality-of-life score will be used for descriptive statistics. The statistical analysis will be performed using SAS 9.4. *P* < .05 is considered statistically significant.

## Discussion

4

HD is a well-defined clinical and pathophysiological placement between benign conditions, but with high impact on quality of life.^[11]^ Bleeding is the main symptom of HD.^[4]^ It is estimated that 50% of people over 50 years of age have experienced symptoms of HD at least once in their life, and one-third of patients affected by HD seek medical attention.^[12,13]^ Excessive bleeding can lead to an emergency situation. Hemorrhoidectomy and stapled hemorrhoidopexy are validated and effective surgical techniques, but are associated with long, painful postoperative courses.^[14]^ Contrary to common belief, a nonsurgical treatment is quite effective to manage HD,^[7]^ which can be offered with expectations of minimal harm.^[6]^ Therefore, medical therapy should be the first-line therapy for this disease.^[5]^

*Liang-Xue-Di-Huang* Decoction has been used to treat HD from the 19th century in China. Rich experience has been accumulated. In 2018, National Administration of Traditional Chinese Medicine of People's Republic of China published 100 classic prescriptions of ancient Chinese medicine, which can be used directly in clinical practice in China. *Liang-Xue-Di-Huang* Decoction was one of 100 classic prescriptions of ancient Chinese medicine. In this classic *Liang-Xue-Di-Huang* Decoction, *Sophora japonica L.* (Huai Jiao) and *Platycladus orientalis(L.)Franco* (Ce Bai Ye) were the Jun (emperor) components. *Sophora japonica L.* (Huai Jiao), which was first recorded in Shen Nong's herbal classic, was commonly applied in clinical practice for the treatment of hematochezia from the 1th century in China. It has the effect of cooling blood, stopping bleeding, clearing heat in bowels and eliminating swell and easing pain.^[15]^ Modern pharmacological studies have demonstrated its efficacy for stopping bleeding and anti-inflammation.^[16]^*Platycladus orientalis(L.)Franco* (Ce Bai Ye) was categorized as a blood cooling and hematostatic herb, which was usually prescribed with heat-clearing herbs to reinforce the efficacy of hemostasis. *Sanguisorba officinalis L.* (Di Yu), *Coptis chinensis Franch*. (Huang Lian), *Rehmannia glutinosa Libosch.* (Sheng Di Huang) were the Chen (minister) components, synergize with Jun to strengthen its therapeutic effects. In traditional Chinese medicine, *Sanguisorba officinalis L.* (Di Yu) was often mixed with other herbs for the treatment of bleeding hemorrhoids. *Coptis chinensis Franch*. (Huang Lian) had the effect of detumescence, clinically used for the treatment of hemorrhoid. *Rehmannia glutinosa Libosch.* (Sheng Di Huang) has been traditionally used as a blood cooling hemostatic. The Zuo (assistant) components, *Angelica sinensis(oliv) Diels.* (Dang Gui), *Citrus aurantium L.* (Zhi Ke), *Scutellaria baicalensis Georgi.* (Huang Qin), *Paeonia lactiflora Pall.* (Chi Shao), *Schizonepeta tenuifolin Briq.* (Jing Jie), and *Trichosanthes Kirilowii Maxim* (Tian Hua Fen), activated blood circulation to remove stasis, eliminated possible adverse effects of the Jun and/or Chen components. The Shi (courier) components, *Cimicifuga heraclei folia.Kom* (Sheng Ma), and *Glycyrrhiza uralensis Fisch.* (Sheng Gan Cao) facilitated the overall action of the other components. Theoretically, *Liang-Xue-Di-Huang* Decoction worked through the traditional Chinese medicine therapeutic principle“Jun-Chen-Zuo-Shi”, to relieve bleeding hemorrhoids and diminish hemorrhoids prolapsed.

Although traditional Chinese medicine has been clinically practiced for thousands of years, most Chinese herbal medicine products do not possess up-to-date regarding about their safety and modern scientific evidences for their claimed clinical uses. To the best of our knowledge, this is the first clinical study to investigate the efficacy and safety of *Liang-Xue-Di-Huang* Decoction in the treatment of HD. If this study confirms that *Liang-Xue-Di-Huang* Decoction is effective and safe, *Liang-Xue-Di-Huang* Decoction could be implemented as a new medical therapy to relieve hemorrhoid bleeding in China and Western countries.

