## Abstract

**Background::**

Hemorrhoidal disease (HD) is one of the commonest proctologic condition in the general population. Medical therapy for HD has not been formally confirmed due to the inconsistent of results. *Liang-Xue-Di-Huang* Decoction, a kind of ancient Chinese classical prescription, has been used to treat HD from the 19th century in China. However, clinical research of *Liang-Xue-Di-Huang* Decoction in the treatment of HD was lack. We designed this study to evaluate the efficacy and safety of *Liang-Xue-Di-Huang* Decoction in the treatment of HD.

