**Table 1 T1:**
[figure not shown]
Standard formulation of *Liang-Xue-Di-Huang* Decoction.

The aim of the present study is to determine: whether *Liang-Xue-Di-Huang* Decoction is useful for relieving HD bleeding, using a randomized, controlled, blind and multicenter trial among officially registered Chinese colorectal consultants, fellows and residents in China.

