### Sample size

2.3

This is a pilot study. In the relevant literature, there are no previous studies utilizing the same evaluation method as the primary outcome to compare a classic prescription.

According to the literature search results, bleeding was used as the primary outcome measure for the treatment of HD by diosmin. It was estimated that *Liang-Xue-Di-Huang* Decoction treatment is not inferior to that of diosmin treatment.

According to the non-inferiority test sample size calculation formula, for a 2-sided significance level of 0.05, the standard deviation is 0.4, (α = 0.05, β = 0.2, δ = 0.15), the non-inferiority bound is 0.15 when the degree of grasp (1−β) = 80%, the sample size is calculated using the formula:

Considering a 10% loss to follow-up, it is expected that 240 patients in over 5 centers (1:1 division into experimental group and control group) will be enrolled and followed up for at least for 7 days.

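### A non-inferiority comparison with diosmin, without a placebo arm or a stated diosmin effect, does not by itself support the conclusion that the decoction is effective

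*Protocol article*

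**What the plan says.** Section 2.3 (Sample size) gives the hypothesis: "It was estimated that *Liang-Xue-Di-Huang* Decoction treatment is not inferior to that of diosmin treatment". Its inputs are a two-sided 0.05 level, an SD of 0.4 and a margin: "the non-inferiority bound is 0.15 when the degree of grasp (1−β) = 80" percent. On the comparator it says only that, in the literature, "bleeding was used as the primary outcome measure for the treatment of HD by diosmin". It reports no size of effect.

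Sections 3.1 and 3.2 describe two arms: decoction with diosmin mimetic, and diosmin with decoction mimetic. No arm receives both mimetics.

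The aim at the end of the Introduction is put in absolute terms: "whether *Liang-Xue-Di-Huang* Decoction is useful for relieving HD bleeding". The last paragraph of the Discussion treats a positive result in the same way: "If this study confirms that *Liang-Xue-Di-Huang* Decoction is effective and safe, *Liang-Xue-Di-Huang* Decoction could be implemented as a new medical therapy".

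On the evidence for drug treatment in general, the abstract states: "Medical therapy for HD has not been formally confirmed due to the inconsistent of results". The Introduction also calls the results inconsistent. The Discussion is more favourable about nonsurgical treatment, but in general terms.

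**The concern.** The comparison answers a relative question: is the decoction no worse than diosmin by more than 0.15? The aim and the closing paragraph ask an absolute one: does it work? Moving from the first to the second needs a further premise, that diosmin beats placebo on this bleeding score, over this period, by more than the margin. The trial cannot check that premise because it has no placebo arm, and the article supplies no figure for it.

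If bleeding settles over 7 days in both arms and diosmin adds little, the arms will look alike whether or not the decoction does anything. A result of no worse than diosmin could then be reported as proof of effectiveness, and the Discussion links that proof to adoption as a new therapy.

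**Working it through.** **Inputs from the article.** Margin 0.15, SD 0.4, two-sided 0.05, 80% power, 10% loss to follow-up, 240 patients allocated 1:1 (section 2.3). Bleeding score range 0 to 9 (Table 2).

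**Assumptions, not in the article.**
- The SD and margin are in points of the bleeding score; section 2.3 states no units.
- A higher score is worse.
- Non-inferiority is declared when the upper limit of the 95% confidence interval for decoction minus diosmin lies below 0.15.
- D, diosmin's true advantage over an inert treatment in this trial, is unknown and is shown as a range.

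**Step 1: the plan's own figure.** n per arm = 2 × [0.4 × (1.960 + 0.842) / 0.15]² = 111.6, so 112 per arm and 224 in total. Allowing for loss, 224 × 1.1 = 246.4 and 224 / 0.9 = 248.9. The stated 240 is close to both. After 10% loss, 240 leaves 216, or 108 per arm, with power 78.7%. A one-sided 0.05 level would need only 88 per arm (about 196 in total after loss), so the stated figure fits the two-sided 0.05 reading.

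**Step 2: chance that an inert decoction passes.** For an inert decoction the true difference from diosmin is D. With 108 per arm, SE = 0.4 × √(2/108) = 0.0544, and

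P(non-inferior) = Φ((0.15 − D)/SE − 1.96).

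| D (points) | (0.15 − D)/0.0544 − 1.96 | P(non-inferior) |
|---|---|---|
| 0 | 0.80 | 78.7% |
| 0.05 | −0.12 | 45.1% |
| 0.10 | −1.04 | 14.9% |
| 0.15 | −1.96 | 2.5% |
| 0.20 | −2.88 | 0.2% |
| 0.30 | −4.72 | below 0.1% |

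At D = 0 the chance equals the trial's power, because an inert decoction and diosmin are then truly equal. With all 120 per arm evaluable, the first four values become 82.8%, 49.1%, 16.1% and 2.5%.

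**Step 3: sensitivity to the SD.** The article gives no source for 0.4. At D = 0 and 108 per arm:
- SD 1.0: SE = 0.1361, P = 19.6%.
- SD 2.0: SE = 0.2722, P = 7.9%.

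A larger SD makes a false success less likely, but at D = 0 it lowers the power to the same figures.

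**The case against.** Five points on the other side deserve weight.

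- **The margin is narrow.** Read as score points, 0.15 is 0.15/9 = 1.7% of the scale. Any true diosmin effect of 0.15 or more holds an inert decoction to a 2.5% chance or less. This stands, and it limits the concern to small diosmin effects.
- **The article is a condensed account.** The derivation of the margin may sit in the full protocol or analysis plan. This also stands: its absence here is not the finding. The finding is that the aim and conclusion printed here go beyond the comparison printed here.
- **The wording is hedged.** The Discussion sentence is conditional, the aim is an open question, and section 2.3 calls the trial a pilot. All true, but the condition is that the study confirms effectiveness, which this comparison cannot do without the missing premise.
- **The Discussion regards nonsurgical treatment as effective.** It does, but it names neither diosmin nor this score nor a 7-day course. Equally, the remarks about inconsistent results concern medical therapy as a class. A reader might infer from them that diosmin does not work; the article does not say so.
- **Non-inferiority as the only test is read from section 2.3.** Section 3.10 names no comparative test. This is correct, and nothing in the article states a superiority hypothesis.

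A reader might also infer that an active-controlled design is wrong here or that a placebo arm is required. The documents do not support that: comparison with a commonly prescribed drug is a legitimate choice, provided the claim matches it.

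**Conclusion.** The point holds as a mismatch between comparison and conclusion. Non-inferiority to diosmin, as set out in this article, does not alone establish that the decoction is effective. This should be fixed, but it does not undermine the trial's planned comparison or its sample size.

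The chance that an inert decoction passes runs from about 79% if diosmin has no effect to near 0 once its effect is clearly above 0.15 points. These figures rest on an SD of 0.4, a margin in score points, 108 evaluable per arm and a 95% confidence interval rule. With an SD of 1.0 the upper figure is about 20%.

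A reader might take the 79% as the expected rate of false success. It is not: it requires a diosmin effect of exactly zero, and nothing in the article indicates that. What can be said is that the risk is real only below about 0.15 points, and that the article gives no figure from which to tell on which side diosmin lies.

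**What to change.** 1. In the aim (end of the Introduction) and the last paragraph of the Discussion, replace usefulness or effectiveness with: non-inferior to diosmin on the bleeding score within the stated margin.
2. State before results are known that a non-inferior result will be reported as: no worse than diosmin; efficacy against no treatment not established. The exception is where the margin is shown to be smaller than diosmin's effect over placebo on a comparable bleeding measure.

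The Discussion paragraph of the abstract speaks only of evaluating efficacy and safety and needs no change.

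The cost is wording and a more modest claim. No patients, visits, procedures or changes to the sample size are needed. Using the exception would take placebo-controlled evidence on diosmin; the article does not show whether its literature search holds any.
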